#### Service-level secondary data sample

No clients will be recruited for the study. We will perform exploratory secondary analyses on routinely collected and anonymised clinical outcomes data and Patient Experience Questionnaires, focusing on those with personality difficulties. This will be defined as scoring 3 or more on the Standardised Assessment of Personality: Abbreviated Scale—Self Report version (SAPAS-SR) [47, 48]. Considering TTad caseloads and estimates of personality disorders in this setting, we estimate that 40 therapists in each site (120 in total) will treat > 20 clients each in a 6-month period before and the 6-month period after the training, creating an estimated sample size of > 4800 service-users (~ 2400 before and ~ 2400 after). Based on previous studies examining the prevalence of personality difficulties in TTad services, we anticipate between 69 and 81% will meet the criteria for probable personality disorder [5, 9] in both pre- and post-training cohorts. The purpose of this secondary analysis will be to determine preliminary proof of concept that the training has the potential to improve service level outcomes for this population and to inform the power calculation for a subsequent randomised definitive evaluation.

#### Recruitment

UK TTad service sites will be recruited through existing links between the research team and UK IAPT services and through the dissemination of a research proposal via the ‘Northern IAPT Practice Research Network’. HICBT therapists working for participating services will be initially approached via email from a service manager who holds the list of eligible therapists 2 weeks before the training intervention. This email will include a link to a participant information sheet and consent form hosted on a survey platform describing the training intervention and the accompanying research. Therapists will be able to attend the training as part of their routine Continued Professional Development provision through their employment regardless of whether they decide to take part in the accompanying research.

### Statistical methods

#### Primary analyses

Primary analyses will address the acceptability and feasibility aims of the study. We will describe the number of UK TTad services recruited to the study, the number (%) of total eligible therapists identified that attend the training in each site, and the number (%) of attending therapists that complete pre-post follow-up surveys. To determine post-intervention views on acceptability, participants’ mean (SD) ratings of intervention theoretical interest, clinical utility, whether it was well presented, and whether they would recommend to other HICBT therapists were rated on a 5-point Likert scale (See Table 1).

We will report the number (%) of cases included in the secondary data extraction with sufficient data for inclusion within the clinical outcome evaluation.

#### Secondary analyses

Secondary analyses of therapist outcomes will focus on both therapist outcomes, including proof-of-concept in attitudinal change, wellbeing, and burnout measures and preliminary proof-of-concept that training has the potential to lead to improvements in clinical outcomes for those with personality difficulties.

#### Therapist outcomes

We will report descriptive statistics (means, standard deviations) to describe the attitudes of therapists before and after the training intervention on each individual rating.

Considering pre to post as our primary outcome for therapist attitudinal change, we will use a series of paired samples two-tailed *t* tests (or an equivalent non-parametric test if that data is not adequately normally distributed) and report effect size (Cohen’s D) to establish preliminary proof of concept that training is significantly associated with positive change in therapist reported confidence to recognise, assess, and triage clients with personality difficulties; formulate clients with these difficulties; anticipate challenges to alliance; and adapt key skills for working therapeutically with these clients, in addition to positive change in attitudes towards working with this group. As a secondary exploratory analysis, we will perform repeated measures ANOVAs including all three timepoints (pre-, post-, and 3-month follow-up).

If we recruit a sufficient sample size (at least 120 × therapists across the 3 sites, with 80% data completion, and therefore 96 complete cases to analyse), we will also use exploratory moderation analyses to explore whether the site, therapist experience (number of years post-qualification), ethnicity (white British vs. other), gender (male/female/non-binary), and experience level moderate the extent of change in attitudes observed during the training.

We will also address whether training has an impact on the rapist-reported wellbeing (SWEMWBS) or workplace burnout (SBI). We will report descriptive statistics to describe the wellbeing and burnout of therapists before and after the training intervention and use paired sample two-tailed tests (or a non-parametric equivalent if data is not adequately normally distributed) to establish if there is significant change in these secondary outcome measures.

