**Routine clinical outcomes on clients with personality difficulties (measured in 6 m before and after the workshop)**		
** Depression symptoms**	Patient Health Questionnaire (PHQ-9 [44];)—a 9-item self-report measure of frequency of depression symptoms (for example, ‘Little interest or pleasure in doing things’). Respondents are asked to rate frequency of symptoms over the past 2 weeks on a 4-point Likert scale from ‘Not at all’ to ‘Nearly every day’. This scale is validated for use in adolescents and adults.	First and last session
** Anxiety symptoms**	The Generalised Anxiety Disorder scale (GAD-7; [45])—a 7-item measure of anxiety symptom (for example, ‘Feeling nervous, anxious or on edge’) frequency over the past 2 weeks, scored on a 4-point Likert scale from ‘Not at all’ to ‘Nearly every day’.	First and last session
** Work and social functioning**	Work and Social Adjustment Scale (WSAS; [46])—a 5-item measure of impairment in daily functioning (for example, ‘Because of my [problem] me ability to work is impaired’) rated on a 9-point Likert scale from ‘Not at all’ to ‘Very severely’.	First and last session
** Measure of personality difficulties**	Standardised Assessment of Personality: Abbreviated Scale—Self Report version (SAPAS-SR; [47, 48])—8-item binary response (yes/no) measure of personality difficulties (for example, ‘In general, do you have difficulty making and keeping friends. This scale is adapted for use as a self-report questionnaire and respondents are asked to indicate ‘Yes’ when the experience applies to them ‘most of the time in most situations’. This scale has been widely used for rapid screening for personality difficulties within the TTad setting for research purposes and has been adopted into routine practice in some services [4, 5, 9].	First session /instance
** Qualitative experiences of treatment**	Patient Experience Questionnaires	Treatment end

**Table 2 Tab2:** Feasibility and acceptability data, method of measurement, and continuation rule to proceed to randomised evaluation without modification

Feasibility/acceptability outcome	Measurement	Continuation rule
**Recruitment**	*Quantitative data*	
	Number of TTad sites recruited to the research project	≥ 3 IAPT sites recruited
	Percentage of eligible therapists attending the training at each site	≥ 60% attendance
	Percentage of attending therapists completing pre- and post-training surveys	≥ 80% data availability

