	Percentage of attending therapists completing 3-month follow-up surveys	≥ 60% data availability
**Acceptability**	*Quantitative data*	
	Feedback data on training (that that the training was theoretically interesting, clinically useful, well presented, and would recommend to other HICBT therapists)	60% agree or strongly agree with each item
	*Qualitative data*	
	Written feedback from therapists on the value of training	No significant concerns emerge about training that cannot be resolved
	Qualitative interviews with therapists	No significant concerns emerge about training that cannot be resolved
	Reporting/identification of serious concerns about the acceptability and feasibility of training by key stakeholders	No serious concerns emerge about training that cannot be resolved
	Reporting/identification of serious negative consequences for therapist participants or the clients they subsequently work with as a result of the training (unexpected, clearly research- or training intervention-related serious adverse reactions).	No serious consequences raised
**Clinical outcome data completion**	*Quantitative data*	
	Percentage of TTad clients receiving routine care during the study with sufficient data for inclusion in secondary analyses (at least one measure of SAPAS-SR personality difficulties and at least × 2 measures of the TTad service minimum dataset [PHQ-9, GAD-7 and WSAS])	≥ 60% data availability
**Proof-of-concept**	*Quantitative data*	
	Therapist attitudinal change in confidence to recognise, assess and triage clients with personality difficulties; to adapt key skills for working therapeutically with this group; and in positivity towards working with this group after completing the training in each service.	Significant improvement from pre to post in all 5 attitudinal domains

In addition to these measures, we will capture clinical data to enable us to generate metrics of engagement including discharge code and number of sessions marked ‘Attended’, ‘Did Not Attend’, and ‘Patient Cancelled’. In line with standard reporting of TTad outcomes, we will also compute the following metrics from clinical outcomes: (i) ‘Recovery’—as defined by moving ≥ 10 to ≤ 9 on the PHQ-9 and from ≥ 8 to ≤ 7 on the GAD-7; (ii) ‘Reliable Improvement’—as defined by improving by ≥ 6 points on the PHQ-9 or ≥ 4 points on the GAD-7; and (iii) ‘Reliable Recovery’—as defined by fulfilling criteria for both ‘recovery’ and ‘reliable improvement’ [49].

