### Sample size

#### Therapists

The final therapist sample size will be determined by the number of therapists participating in the training at each of the three participating sites. Based on our previous experience, we anticipate that approximately 40 therapists will attend at each site (120 total). Based on similar studies examining the effects of training for healthcare professionals on attitudes and behaviours (e.g. [52, 53]), we anticipate the effect size of training on change in therapist attitudes and perceived self-efficacy to work with this client group to be at least *d* = 0.4. A G*Power [54] calculation indicates that the required sample size to detect a medium effect of *d* = 0.4 in a paired samples two-tailed *t* test, with 80% power is *n* = 84. Assuming 120 therapists attend the training, with 80% data completion, we will have 96 participants to analyse. This is sufficient power to detect a small-medium (*d* ≥ 0.27) pre-post effect size on these therapist ratings.

A sub-sample of therapist participants will be invited to take part in an in-depth qualitative interview about their experiences of the training. We anticipate undertaking up to 20 interviews, guided by ‘data saturation/information power’ relevant to the study objectives.

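### The exploratory three-timepoint attitude analysis uses repeated measures ANOVA, which at the plan's minimum completion targets keeps at most 72 of the 96 therapists with pre and post data; a mixed model on all ratings is a free improvement

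*Protocol article*

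**What the plan says.** The Therapist outcomes section makes pre to post the main attitudinal comparison: "Considering pre to post as our primary outcome for therapist attitudinal change, we will use a series of paired samples two-tailed" t tests, or a non-parametric equivalent. It then adds the three-wave analysis, labelled secondary and exploratory: "we will perform repeated measures ANOVAs including all three timepoints (pre-, post-, and 3-month follow-up". Table 1 lists the attitude questionnaire at all three timepoints.

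The numbers come from two places. The Sample size section states "we anticipate that approximately 40 therapists will attend at each site (120 total" and "Assuming 120 therapists attend the training, with 80% data completion, we will have 96 participants to analyse". Table 2 sets two completion thresholds:

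- "Percentage of attending therapists completing pre- and post-training surveys": at least 80%.
- "Percentage of attending therapists completing 3-month follow-up surveys": at least 60%.

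The attitudinal continuation rule in Table 2 concerns pre-to-post change only. The article names no mixed model, imputation or other handling of missing therapist surveys for the three-wave analysis. All quantitative analyses are to be done in SPSS or R.

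**The concern.** The plan accepts lower completion at 3 months than at pre and post, so incomplete rows are to be expected. The named method conventionally drops every therapist with any wave missing. The change from pre-training to 3 months would then be estimated only in therapists who answered all three surveys. In general that is unbiased only if the missing surveys are missing completely at random, that is, unrelated to attitudes or to how much they changed.

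Most therapists lost at 3 months will probably already have given pre and post ratings. Those ratings carry information about whether the lost therapists differ from the rest, and the ANOVA discards it.

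What is at stake is the plan's only named quantitative test of the 3-month attitude ratings. A smaller point is that the ANOVA's pre-post component will rest on a different sample from the paired t tests. One report could then carry two pre-post estimates that differ without explanation.

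**Working it through.** **Inputs.** Attending: 120 (Sample size, Therapists). Completed pre and post: 80% (Table 2). Completed 3-month survey: 60% (Table 2). Both percentages are of attending therapists, so they share a denominator.

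**The plan's own figure.** 120 × 0.80 = 96, which reproduces the stated 96.

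**Follow-up responders.** 120 × 0.60 = 72.

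**Therapists with all three surveys.** This is the overlap of the 96 and the 72 among the same 120 people.

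| Overlap | Formula | All three surveys | Lost from the 96 |
|---|---|---|---|
| Maximum (every follow-up responder has pre and post) | min(96, 72) | 72 | 24 (25%) |
| Independent response | 120 × 0.8 × 0.6 | 57.6, about 58 | 38.4 (40%) |
| Logical minimum | 96 + 72 − 120 | 48 | 48 (50%) |

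The minimum requires all 24 therapists who lack a pre or post survey to answer at 3 months. That is possible but unlikely, so the loss is likelier to lie between 25% and 40%.

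**What a mixed model gains for the pre-to-3-month contrast.** Take the maximum-overlap case: 72 therapists with all three ratings and 24 with pre and post only. Assume equal variance 1 at each wave and a common correlation r between waves; the protocol gives no values.

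- Variance of the individual change: T = 2(1 − r).
- Part not explained by the pre and post ratings: R = 1 − 2r²/(1 + r).
- Explained part: E = T − R.
- ANOVA on completers: variance of the mean change = T/72.
- Mixed model (large-sample): variance = E/96 + R/72.
- Ratio of variances: (0.75E + R)/T.

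| r | T | R | E | Variance ratio | Standard error ratio |
|---|---|---|---|---|---|
| 0.3 | 1.400 | 0.862 | 0.538 | 0.904 | 0.951 |
| 0.5 | 1.000 | 0.667 | 0.333 | 0.917 | 0.957 |
| 0.7 | 0.600 | 0.424 | 0.176 | 0.926 | 0.963 |

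The standard error falls by about 4% to 5%. The gain would be larger with less overlap.

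**The case against.** **The analysis is exploratory and no primary result is lost.** This stands. The paired t tests keep all 96 therapists, and so does the attitudinal continuation rule. A reader might infer that a quarter to a half of the pre-post evidence is thrown away, or that pre-post power drops. With two-sided alpha 0.05 (assumed, as the protocol states none), the detectable d at 80% power would go from 0.289 at n = 96 to 0.335 at 72, 0.376 at about 58 and 0.413 at 48. Those figures describe a contrast that the plan tests elsewhere on the full sample, so they do not measure any harm here. (The protocol states 0.27 for n = 96; that difference is a separate matter and does not touch the counts above.)

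**The targets are minimums.** This also stands. The thresholds are continuation rules, not forecasts, and better follow-up shrinks the loss.

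**No method creates missing 3-month ratings.** True. At 60% there are 72 of them whatever model is used, and at maximum overlap the ANOVA already uses every one. The precision gain is therefore small.

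**The direction of bias.** It is tempting to say that therapists who found the workshop less useful will not reply, so that completers overstate how well gains last. The protocol says nothing on reasons for non-response, and this cannot be claimed. Nor does it list durability of attitude change as an objective or tie a continuation rule to it.

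**Missing-data handling belongs in the fuller documents.** This does not dispose of the point. Listwise deletion is not written in the article, but the method is, and the complete-row requirement follows from how that method is conventionally run. The comment is on a stated choice, not on an omitted detail.

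**Conclusion.** The point holds as an improvement to a secondary exploratory analysis. At the plan's minimum completion targets and 120 attendees, conventional repeated measures ANOVA keeps 48 to 72 of the 96 therapists with pre and post data. The loss is 25% at best, 40% under independent response, and 50% only as a logical bound.

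The main reason to change is the weaker assumption, not precision. A likelihood-based mixed model is valid if non-response is explained by the ratings already observed, whereas the completers-only ANOVA generally needs non-response to be unrelated to attitudes and their change. Whether bias would arise, and in which direction, cannot be told from the document. If non-response depends on unobserved 3-month attitudes, both methods are biased.

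The conclusion rests on the ANOVA being run in the conventional complete-row way and on completion near the stated minimums. The sample size, the primary pre-post tests and the continuation decision do not change.

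**What to change.** In the Therapist outcomes section, replace the repeated measures ANOVAs with a linear mixed model for repeated measures for each attitude item. Use time as a three-level factor, site as a fixed effect, an unstructured within-therapist covariance, REML and all available ratings. Report the pre-to-post and pre-to-3-month contrasts with 95% confidence intervals. Keep the complete-case ANOVA as a sensitivity check, and give the number of therapists contributing to each analysis so that any difference from the paired t tests can be understood.

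Add one sentence stating that the model is valid under missing at random and does not correct for non-response that depends on unobserved 3-month attitudes. Also say that the precision gain for the pre-to-3-month contrast is expected to be modest if follow-up responders are mostly pre-post completers.

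The cost is a change of wording. No new data, survey wave or sample size is needed, and both SPSS and R fit the model.

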#### Clinical outcomes

We will report descriptive statistics (means, standard deviations) to describe the clinical measures and client characteristics at intake within the pre- and post-training intervention cohorts (those engaging in treatment in the 6 months pre- compared to 6 months post-therapist training). This will include PHQ-9, GAD-7, and WSAS mean scores; the proportion of clients showing mild, moderate, and severe cut-offs on each scale; and the proportion of clients scoring 3 or more on the SAPAS-SR (indicative of personality difficulties).

This research is a multi-site observational study prior to conducting a definitive evaluation with a randomised trial and therefore has not been a priori powered to inferentially examine between cohort differences in clinical outcomes. However, it is both possible and useful to estimate the between-cohort effect size (and their 95% confidence interval) on client outcomes to help inform decisions to continue to a definitive evaluation of the training intervention and to inform future power calculations. We will therefore report the observed effect sizes but not *p* values. These analyses will focus solely on the subgroup of participants meeting the criteria for probable personality disorder (3 or more on the SAPAS-SR), which we estimate from previous research to be between 69 and 81% of client treatments [5, 9]. A series of linear regressions will examine whether treatment-cohort (treated before or after training) predicts the number of treatment sessions attended and post-treatment levels of depression (PHQ-9), anxiety (GAD-7), and functioning (WSAS). All analyses will include the training site as a covariate. The post-treatment analyses will adjust for the pre-treatment level of the relevant variable. Comparable binary logistic regressions will examine binary outcomes (rates of reliable improvement, recovery, and reliable recovery; rates of clients with planned discharges), again seeing if the treatment cohort (before or after training) predicts each variable and covarying for the training site. As we do not anticipate sufficient statistical power to do inferential statistics, we will examine the distribution of effect sizes, potentially using confidence intervals and Bayesian methods relative to estimates of minimum clinically important difference on clinical outcomes (cf., [55–58]). All quantitative analyses will take place in SPSS or R.

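### The client models carry no therapist term, so the 95% CIs may be mis-sized in either direction and the therapist-level ICC needed to plan the next trial is not estimated

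*Protocol article*

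**What the plan says.** In the protocol article, Statistical methods, Clinical outcomes, linear regressions on cohort are planned for sessions attended and for post-treatment PHQ-9, GAD-7 and WSAS, the last three adjusted for their pre-treatment value. Logistic regressions on cohort are planned for the binary outcomes. The grouping term is fixed in one sentence: "All analyses will include the training site as a covariate". Effect sizes with 95% CIs are to be reported without p values, and Bayesian methods are mentioned as a possibility.

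Under Sample size, Service-level secondary data sample, the client numbers are built up through therapists: "40 therapists in each site (120 in total) will treat" more than "20 clients each in a 6-month period before and the 6-month period after the training", giving more than "4800 service-users". Only clients scoring 3 or more on the SAPAS-SR are analysed: "we anticipate between 69 and 81% will meet the criteria for probable personality disorder". One stated purpose is "to inform the power calculation for a subsequent randomised definitive evaluation".

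The article mentions no therapist effect, clustered standard errors, intracluster correlation or therapist identifier in the client data.

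**The concern.** The workshop acts on therapists, and each therapist contributes many clients. Clients of one therapist tend to have correlated outcomes. A fixed effect for three or so sites does not remove that correlation, because it sits one level below site.

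Two things are at stake. First, a model that treats clients as independent gives CIs of the wrong width, and the plan intends to read those CIs against minimum clinically important differences. Second, a later randomised evaluation of therapist training has to allow for clients being nested in therapists. This study, with about 120 therapists observed in two periods, is well placed to estimate the correlation concerned, but the planned models do not yield it.

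This is not a detail left to a fuller document. The article states model type, covariates and grouping term, and therapist is not among them.

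**Working it through.** **The plan's own figure.** 120 therapists × 20 clients × 2 periods = 4800, or 2400 per cohort. This reproduces exactly.

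**Analysed clients per therapist per period (m).** 20 × 0.69 = 13.8 and 20 × 0.81 = 16.2, which is 1656 to 1944 clients per cohort. Table 2 accepts "60% data availability" for client outcomes. At that floor m is 13.8 × 0.6 = 8.3 to 16.2 × 0.6 = 9.7. The plan expects more than 20 clients, so m could also be larger.

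**Formula for the CIs.** If the same therapists treat m clients in each period, the true variance of the cohort difference divided by the variance under independence is

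VR = 1 + (m − 1) × ICC − m × ICC × CAC

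where CAC is the between-period correlation of a therapist's effect. The true standard error is √VR times the reported one, and the coverage of a nominal 95% CI is 2Φ(1.96/√VR) − 1. The article gives neither ICC nor CAC; both are assumptions here.

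**Worked example.** ICC 0.05, CAC 0.5, m = 13.8: 1 + 12.8 × 0.05 − 13.8 × 0.05 × 0.5 = 1.295, and √1.295 = 1.14. For m = 16.2: 1 + 15.2 × 0.05 − 16.2 × 0.05 × 0.5 = 1.355, and √1.355 = 1.16.

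**Results at ICC 0.05, m = 13.8 to 16.2:**

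| CAC | VR | True SE / reported SE | Coverage of nominal 95% CI |
|---|---|---|---|
| 1 | 0.95 | 0.97 | 95.6% |
| 0.8 | 1.09–1.11 | 1.04–1.06 | 94% |
| 0.5 | 1.30–1.35 | 1.14–1.16 | 91–92% |
| 0 | 1.64–1.76 | 1.28–1.33 | 86–87% |

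A simulation with 120 therapists, 3 sites, m = 15, ICC 0.05, and ordinary regression on cohort and site gave coverage of 94.9%, 93.9%, 91.2% and 86.7% for the four rows, in line with the formula.

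**Other ICCs (same m).** At ICC 0.02 the SE ratio runs from 0.99 (CAC 1) to 1.12–1.14 (CAC 0). At ICC 0.10 it runs from 0.95 to 1.51–1.59.

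**At the 60% data floor (m = 8.3 to 9.7, ICC 0.05).** CAC 0.8 gives VR 1.03–1.05, a ratio of about 1.02. CAC 0.5 gives VR 1.16–1.19, a ratio of 1.08–1.09.

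**The planning input.** If the next trial randomised therapists and measured 15 clients per therapist, its size relative to individual randomisation would be 1 + 14 × ICC: 1.28 at ICC 0.02, 1.70 at 0.05 and 2.12 at 0.08. An uncertain ICC within this assumed range therefore changes the required number of clients by a factor of 2.12/1.28 = 1.7.

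**The case against.** The client analyses are labelled exploratory, the article says they are not powered for inference, and no continuation rule in Table 2 depends on a client effect. A CI that is a few per cent off crosses no formal threshold. This stands, and it limits how much weight the CI point can bear.

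Three stronger readings are tempting, and the article does not support them.

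- *A reader might infer that the CIs are simply wrong, or too narrow by the full factor 1 + (m − 1) × ICC.* Largely the same therapists appear in both cohorts, so a stable therapist effect cancels and the CI becomes slightly too wide. The direction depends on a between-period correlation that nobody yet knows. Turnover of therapists, or a training effect that varies between them, would push towards intervals that are too narrow.
- *A reader might infer that the power-planning purpose is not met.* Effect sizes, outcome spread, event rates and data completeness also inform a power calculation, and the plan will deliver them. One key input is missing. The article does not say whether the next trial will randomise therapists, services or clients. If services, the therapist ICC alone would not suffice, and about three sites cannot give a usable service-level one.
- *A reader might infer that clients of untrained therapists dilute the after-training cohort,* because the rule on "Percentage of eligible therapists attending the training at each site" accepts 60%. The article uses the same 40 per site and 120 in total for expected attendees and for treating therapists, which points towards attendees' clients. It does not state the extract rule, and silence on this in an article is not an error. It also names service-level outcomes as a target, for which partial attendance would be part of the effect.

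**Conclusion.** The concern holds in limited form. The specified client models leave out the level at which the training acts. For this study's CIs the consequence may be modest: at an assumed ICC of 0.05, from 3% too wide (CAC 1), through 4–6% too narrow in standard-error terms at CAC 0.8, to 14–16% at CAC 0.5, and less if client data are near the 60% floor. These figures rest on assumed ICC and CAC values, equal caseloads and the same therapists in both periods.

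The missing therapist ICC and between-period correlation is the firmer consequence. It follows from the stated models whatever the true ICC is, and it bears on a purpose that the article itself sets. This should be put right before the client data are requested: the data are to be anonymised, so a therapist link left out at extraction may not be recoverable.

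**What to change.** Request a pseudonymised therapist code in the client extract. Replace the ordinary regressions with mixed linear and mixed logistic models that have a random therapist intercept and a random therapist-by-cohort effect, keeping site as a fixed effect and the planned baseline adjustment. Report the therapist ICC and the between-period correlation, each with a CI, beside the cohort effect sizes.

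Therapist-clustered standard errors are an acceptable simpler route to the CIs, but they do not produce an ICC, so a variance-components estimate would have to be added.

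The analysis cost is small, since R is already an allowed package. The real cost is a data-governance step. Therapists may attend the training without joining the research, so a code that links client outcomes to therapists, even pseudonymised, needs to be cleared with the services. If it cannot be obtained, the report should say that the CIs assume independent clients and that the planning ICC must come from elsewhere.
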